#### **LEAP-MS coaching sessions**

LEAP-MS participants will meet with an intervention physiotherapist up to six times, remotely or face-face in their own homes. During coaching sessions, participants will be shown how to navigate and use the LEAP-MS online platform as required, select suitable activities, form an activity plan and set and review activity goals. Drawing on both their professional knowledge and training underpinned by the Bridges self-management approach [61], people with MS are taught how to utilise self-efficacious and self-regulatory practices throughout the consultations. Critically, physiotherapists will not instruct, or prescribe activity to participants—but instead use coaching techniques and open questioning to consider meaningful activities they would like to try and support participants to set goals, log activity and monitor their progress. Through discussion, physiotherapists will support participants to identify potential barriers (e.g. their own motivation, habits, environmental or social factors) and pre-plan ways to overcome these barriers should they arise. Following a mandatory initial coaching session, participants will be able to request up to five further coaching sessions and/or communicate via a messaging function described below.

#### **Participant use of the LEAP-MS platform and interaction with physiotherapists**

In the initial 3-month intervention period, participant use of the LEAP-MS platform works in conjunction with support from intervention-trained physiotherapists and includes a user pairing facility where patient users are paired with an intervention physiotherapist. The physiotherapist can view the activity selections and goals set by the patient participant and provide coaching and support to engage with participants in setting small targets and incorporating physical activity into their everyday life. The web-based platform also has an in-built messaging function to enable participants to contact their physiotherapist in the initial 3-month period to ask questions, seek guidance about activity engagement and request up to six coaching sessions. Coaching sessions will be conducted at participant’s homes or online dependent on participant preference whilst accommodating any local restrictions (e.g. social distancing during COVID-19 or staff availability—see [62] for COVID-19 study adaptations). When conducted online, coaching sessions will be conducted via a secure web video conferencing system. All interactions (whether in person, via web video conferencing or via the in-built platform messaging system) will operationalise a supported self-management approach to regular physical activity. Physiotherapists will not be required to respond immediately to communication through the platform, but will schedule regular time slots to respond to LEAP-MS communication, as they would with other forms of patient communication—such as returning telephone calls from outpatients or family members. They will aim to respond within 5 working days. A pre-specified inactivity period of 21 days on the website by any one participant will automatically be logged and flagged to the corresponding patient participant’s physiotherapist, who will then contact the participant to offer any further support.

Interactions between participant and physiotherapist using the in-built platform messaging function will be captured by the study database. Notes of coaching sessions will be recorded in the web platform and downloaded for adding to patient notes. Where face-to-face coaching sessions are conducted, intervention physiotherapists will be required to detail distance travelled, mode of travel time and face-to-face contact time. For coaching sessions delivered via web video conferencing, only video conferencing time will be detailed.

#### **Physiotherapist training**

All intervention physiotherapists will receive bespoke LEAP-MS training, which delivers (1) real-time training (either face-face or remotely) about self-management principles and how to integrate these into contacts with patients, (2) how to use online conferencing as a method of communication and providing consultations, (3) how to introduce/instruct patients in the use of online conferencing and online resources (in this case the LEAP-MS platform) and (4) a clinical update on physical activity and exercise guidelines for use with people with neurological conditions. The training package consists of real-time training days (delivered face-face or remotely) and an online self-study resource. The real-time self-management training workshops are delivered by experienced facilitators from Bridges Self-Management (http://www.bridgesselfmanagement.org.uk/). Paper-based learning materials traditionally accompanying face-face training workshops and video-recorded films from the training have been digitised and housed in an online learning platform for use by intervention physiotherapists to refer back to as required. Given the emergent challenges in rehabilitation service delivery during the COVID-19 pandemic, and the anticipated move to greater use of remote intervention delivery, further resources (https://www.bridgesselfmanagement.org.uk/covid-19-resources/) to help structure remote interactions were also made available as part of the final training package to ensure standardisation of coaching interactions regardless of the mode of delivery (online or face to face in the home). In addition, an accompanying online training resource included video-recordings with experienced physiotherapists with expertise in the use of digital technologies in practice to provide guidance on the use of technology in coaching sessions and videos with an expert in exercise prescription for people with neurological conditions to teach core principles of exercise physiology and prescription [63, 64]. Intervention physiotherapists are required to watch and work through these additional learning materials independently.

The physiotherapists who complete the training will be invited to participate in the LEAP-MS study as ‘intervention physiotherapists’. All those who consent to taking part will have access to conversation-based scripts that they can use to guide their coaching conversations (primarily for online use). They will also have the opportunity to practice coaching conversations and receive peer review. They will be asked to take part in interviews to share their experience of intervention training and intervention delivery.

#### **Safety**

We will assess and record any adverse events that may be reported.

##### Expected adverse events (AEs)

In this patient population, hospitalisation due to MS, acute illness resulting in hospitalisation, new medical problems and deterioration of existing medical problems are expected. This information will be self-reported by patients online and will not be subject to expedited reporting; however, it will be reviewed on a monthly basis by the study team. The physical activity intervention does not specifically involve any heavy load-bearing exercise or heavy eccentric muscle activity. However, some minor muscle soreness or muscular strain may occur in the few days following the initiation of a new exercise programme or increased physical activity. This would normally resolve spontaneously and would not require any specific interventions or additional medical care but will be noted as a potential expected related AE if reported during the 3-month intervention period. Falls and fatigue are an expected AE as part of the clinical condition but will be monitored for the duration of the intervention.

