##### Procedure

Participants will be asked to use the LEAP-MS platform to self-report any incidents of falls, fatigue, increased muscle soreness or sprain, or other incidents they feel are relevant, and whether the incident required medical intervention. Selecting that medical intervention was required will trigger an automated prompt to the paired physiotherapist. Similarly, no activity on the online platform for 3 weeks will also trigger an automated prompt to the paired physiotherapist. Once prompted, the paired physiotherapist will contact the participant to discuss the incident. All serious adverse events (SAEs) that occur between the time of consent and the 3-month follow-up must be reported immediately to the Centre for Trials Research (within 24 h of knowledge of the event) by the intervention therapist using a dedicated SAE form, unless the SAE is specified as not requiring immediate reporting.

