Intervention uptake and safety are not formal progression criteria in this single-arm feasibility study but will be closely monitored and considered in any final recommendations for further evaluations. Intervention uptake will be reflected by (1) the percentage of initial coaching sessions completed, the number of additional physiotherapy coaching sessions requested and completed and the number of remote physiotherapist contacts recorded and (2) frequency and duration of weekly logged physical activity. Website log in rates and length of time between each log in episode will provide supplemental information on intervention uptake. Safety will be assessed using an online process of self-reporting by the participant and from any SAE forms completed by the intervention therapist.

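### Falls and fatigue are ascribed in advance to MS, with no potentially-related category such as soreness has, and no relatedness record is described for those needing no medical care

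*Protocol article*

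**What the plan says.** The Expected adverse events (AEs) section of the protocol article treats two groups of events differently in one paragraph. Minor muscle soreness or strain "may occur in the few days following the initiation of a new exercise programme or increased physical activity", and such an event "will be noted as a potential expected related AE if reported during the 3-month intervention period". For the other group the wording is: "Falls and fatigue are an expected AE as part of the clinical condition but will be monitored for the duration of the intervention".

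The Procedure section sets out the participant's task as follows: "self-report any incidents of falls, fatigue, increased muscle soreness or sprain, or other incidents they feel are relevant, and whether the incident required medical intervention". It then says: "Selecting that medical intervention was required will trigger an automated prompt to the paired physiotherapist". The follow-up step is: "Once prompted, the paired physiotherapist will contact the participant to discuss the incident". A second automated prompt follows three weeks without platform activity. Serious adverse events go on a dedicated form.

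Planned analyses lists safety with recruitment, retention and uptake as the primary objectives. It adds that safety is not a formal progression criterion but will be weighed in the final recommendations. On the source of the data it says: "Safety will be assessed using an online process of self-reporting by the participant", together with any SAE forms.

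**The concern.** The paragraph uses both a related category and a time reference, but applies them only to soreness and strain. Falls and fatigue are tied to the disease before any event has been seen.

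That sits badly with the rest of the article. Under Assessments, the intervention is hypothesised to reduce fatigue impact on the MFIS, so an improvement in fatigue would be read as a possible intervention effect while a reported worsening is ascribed to MS. For falls, the activity suite includes balance work, aerobics and tai chi. The population has EDSS 6 to 8, and participants choose their own activities rather than having them prescribed. A fall during such an activity is a plausible intervention harm.

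With no comparator and no stated background rate, information on the individual event is the main means of telling activity-connected events from background ones. If it is not recorded and tabulated, the totals of falls and fatigue say little about the safety of the intervention, and the pre-stated attribution invites the reader to put them all down to MS.

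**Working it through.** No figure in the article bears on this point. The sample size of 21 rests on the precision of the recruitment proportion: 1.96² × 0.7 × 0.3 / 0.2² = 20.17, rounded up to 21. Nothing about safety enters it. The check is therefore mainly a comparison of the text.

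1. **Classification (Expected adverse events).** Soreness or strain: expected and potentially related, with a reference to the days after new or increased activity. Falls and fatigue: expected, as part of the condition, and monitored. No related category and no time reference are given for them.

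2. **Content of the report (Procedure).** The article describes two elements: the incident, and whether it needed medical intervention. It mentions no date, circumstance or relatedness item. This is a one-sentence summary and does not claim to list every field.

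3. **Route to individual assessment (Procedure).**
   - Medical intervention selected: prompt, then discussion with the physiotherapist.
   - Serious event: SAE form.
   - Fall or fatigue episode needing no care: no step described. The inactivity prompt depends on platform use, not on the incident.
   - The monthly study-team review is attached to self-reported hospitalisations, new problems and deteriorations, with no relatedness judgement mentioned.

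4. **Consequence for the safety summary.** Combining 1 and 3, a fall during a LEAP-MS activity that needed no care would be counted in the same way as a fall unconnected with any activity.

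5. **Which timing item would discriminate.** Assume that the few days after activity means 2 to 4 days.
   - Active once a week: the activity day plus 2 to 4 further days covers 3 to 5 of 7 days.
   - Active on Monday, Wednesday and Friday: a window of only 2 days already covers 7 of 7.

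   In a regularly active participant almost any event falls in the window, whatever its cause. An item on whether the event happened during an activity does not have this problem.

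6. **What 21 people can show.** If no participant had an activity-connected fall, the exact two-sided 95% upper limit would be 1 − 0.025^(1/21) = 16.1%. If 5 of 21 had one (an assumed count), the interval would be 8.2% to 47.2%. Better recording makes the table interpretable but does not make it precise.

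**The case against.** The strongest objection is that this is a condensed article drafted from a full trial protocol that is not shown. The fields of the incident form and the causality procedure for non-serious events are details that such an article commonly leaves to that document. This stands as far as it goes: a reader might infer that the form asks nothing about timing, and the article does not establish that.

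Second, expected is a statement about anticipation, not causality. A reader might infer that falls and fatigue are formally classed as unrelated. No sentence says so or bars a relatedness judgement, and both events are solicited by name. That stands too. What it does not explain is why the same paragraph gives soreness a related category and ties falls and fatigue to the condition. That contrast is stated text, not silence.

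Third, a reader might infer that these events cannot be linked to the intervention at all. That is too strong. Incidents are reported on the platform that holds the activity log. Messages and session notes are captured, participants can raise an incident in a message or coaching session, and those who consent are interviewed at 3 months. Matching reports to logs would, however, need dated reports, and the article describes no such matching; the activity summary it names is weekly frequency and duration.

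Finally, safety is not a formal progression criterion, and the only harm the article itself links to increased activity is soreness or strain. Both are true. They limit the weight of the point, but safety remains a primary objective and feeds the recommendations.

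**Conclusion.** The point holds as one about stated attribution and described recording. The article ascribes falls and fatigue to the clinical condition without the potentially-related category it gives to soreness or strain, and it describes no relatedness record for non-serious events that needed no medical care. The safety summary would then give counts of falls and fatigue that do not separate events connected with LEAP-MS activity from the rest.

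The size cannot be stated as a count or percentage, since the article gives no rate of falls or fatigue and no share needing medical care. The gap covers all falls and fatigue reports that needed none.

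The conclusion assumes that the full protocol and form contain no contrary rule. If date and relatedness fields already exist, what remains is to align the classification with them and to use them in the safety table. It is worth correcting, but it does not threaten the formal progression criteria.

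**What to change.** 1. In Expected adverse events, treat falls and fatigue as events that may be related to the intervention, on the same footing as soreness or strain. They can remain expected.
2. In Procedure, have the existing online incident report record the event date and whether the event happened during a LEAP-MS activity. If these fields already exist in the full protocol or form, state that and use them, supported by the activity log.
3. In Planned analyses, tabulate falls, fatigue and soreness or strain by that item. Report any category for the days after an activity separately, because it will not discriminate in regularly active participants.

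The cost is at most two fields on a form that participants already complete, and one further split in the safety table. The downside is self-reported timing with recall error, and evidence on causation that stays descriptive in 21 people without a comparator. The change concerns recording and reporting only; it does not alter how falls or fatigue are managed.

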##### Procedure

Participants will be asked to use the LEAP-MS platform to self-report any incidents of falls, fatigue, increased muscle soreness or sprain, or other incidents they feel are relevant, and whether the incident required medical intervention. Selecting that medical intervention was required will trigger an automated prompt to the paired physiotherapist. Similarly, no activity on the online platform for 3 weeks will also trigger an automated prompt to the paired physiotherapist. Once prompted, the paired physiotherapist will contact the participant to discuss the incident. All serious adverse events (SAEs) that occur between the time of consent and the 3-month follow-up must be reported immediately to the Centre for Trials Research (within 24 h of knowledge of the event) by the intervention therapist using a dedicated SAE form, unless the SAE is specified as not requiring immediate reporting.

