**Assessments**						
MFIS		X			X	X
MSIS-29		X			X	X
EQ-5D-5L		X			X	X
OxPAQ		X			X	X
UW-SES-SF		X			X	X
PGIC					X	X
Semi-structured interview					X	

After the baseline assessments have been completed by the participant, their online user account will be paired with an intervention physiotherapist’s account. This physiotherapist will then contact the participant to arrange the first coaching session, after which the full LEAP-MS online tool will be released to the participant.

Participants will be asked to repeat the online patient-reported outcome measures, plus a modified Patients’ Global Impression of Change (PGIC) [60], at 3 months and 6 months post-baseline. In this, they will be asked to indicate their degree of change using one of five responses (much better, slightly better, the same, slightly worse, much worse) in relation to their routine activities, emotional well-being and social engagement.

Automatic prompts will be provided to the registration email address at the start of the follow-up data collection window (2 weeks before and 2 weeks after the expected assessment completion date). Participants will receive a telephone reminder if they have not logged on in the 2 weeks prior to the expected assessment completion date. Electronic data capture will be standardised across all study remote processes using an online platform developed by the Centre for Trials Research using a bespoke Structured Query Language (SQL) database. A study-specific data management plan has been developed to ensure the security and confidentiality of all participant data and that high-quality data is available for ongoing analyses.

At the end of the initial intervention period (3 months), participants and their treating physiotherapists will be asked to participate in a semi-structured interview aimed at eliciting experiences and reflections on the intervention, and the process of its delivery (content, design, language, adaptability to personal needs and recommendations for the future). Given the small sample size of this feasibility study, everyone who consents to being interviewed will be interviewed, even if they withdraw from the intervention (see the ‘Process evaluation’ section). Interviews will be conducted by a research team member who is not involved in the intervention delivery but is a physiotherapist by background and an experienced qualitative researcher.

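### Non-serious adverse events and expected hospitalisations are recorded through self-report on the intervention platform, with no scheduled adverse-event question, so participants who stop using it are likely to be under-counted

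*Protocol article*

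**What the plan says.** The Safety section (Procedure) gives the main route: "Participants will be asked to use the LEAP-MS platform to self-report any incidents of falls", together with fatigue, muscle complaints and anything else the participant thinks relevant. Expected adverse events (AEs) sends hospitalisation due to MS, acute illness leading to hospitalisation, and new or worsening medical problems to online self-report as well. These are reviewed monthly and are not expedited.

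Planned analyses names the sources of safety data: "Safety will be assessed using an online process of self-reporting by the participant and from any SAE forms completed by the intervention therapist". The therapist must report a serious event within 24 hours of learning of it. This applies from consent to the 3-month follow-up, and some serious events are exempt from immediate reporting.

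There is a safeguard for people who go quiet. Procedure says that "no activity on the online platform for 3 weeks will also trigger an automated prompt to the paired physiotherapist", and then: "Once prompted, the paired physiotherapist will contact the participant to discuss the incident". The section on participant use of the platform describes the same 21-day flag but gives the contact another purpose. There it goes to the physiotherapist, "who will then contact the participant to offer any further support".

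Table 1 lists five questionnaires at baseline, 3 and 6 months, the global impression of change at 3 and 6 months, and an interview at 3 months. It has no adverse-event row.

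**The concern.** The platform is both the intervention and the main instrument for recording harm. A participant who stops logging in stops supplying safety data through the main route. A fall, worse fatigue or an admission is a plausible reason to stop, so missing reports may come disproportionately from people who had events.

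The other listed source covers serious events only and needs the therapist to learn of them. Only the first coaching session is mandatory, so later clinician contact is not assured. An expected hospital admission in someone who has stopped logging in could be absent from both sources.

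Safety is one of the four quantitative measures in the primary objectives, and it will be weighed in the recommendation on further evaluation. A low count could reflect few events or few reports, and the data as planned would not separate the two.

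**Working it through.** **What the article supplies.** It gives the sample size (21), the recording routes, the 21-day flag and the schedule. It gives no event rate, no expected share who stop using the platform, and no capture rate among them. There is no figure of the plan's own to reproduce on this point, so everything numerical below is an assumption shown over a range.

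**Does the inactivity contact close the gap?** Three places bear on it:

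- Safety, Procedure: the contact is to discuss an incident. That fits a participant who has reported needing medical care, but a participant flagged only for inactivity has reported nothing.
- Participant use of the platform: the contact is to offer support.
- Planned analyses: the safety sources are online self-report and serious-event forms. The inactivity contact is not among them.

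Events could come to light at the contact, but nothing written requires the physiotherapist to ask about them or says where a non-serious event would be entered. The platform-use section describes physiotherapist pairing and messaging for the initial 3 months, while platform access runs to 6 months. It does not say whether the flag continues after month 3.

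**Size under equal true risk.** Let f be the share who stop using the platform and r their event capture relative to users, taking capture among users as complete. Then

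observed / true = (1 − f) + f·r = 1 − f(1 − r).

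| Assumed f | r = 0 | r = 0.5 | r = 1 |
|---|---|---|---|
| 10% | 0.90 | 0.95 | 1.00 |
| 30% | 0.70 | 0.85 | 1.00 |
| 50% | 0.50 | 0.75 | 1.00 |

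For example, with f = 30% a true proportion of 40% would be recorded as 0.40 × 0.70 = 28% (r = 0), 0.40 × 0.85 = 34% (r = 0.5) or 40% (r = 1).

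**Size if those who stop have more events.** Assume 15 of the 21 stay engaged with 30% having an event, and 6 stop with 50% having one.

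- True: (15 × 0.30 + 6 × 0.50)/21 = 7.5/21 = 36%.
- Recorded, r = 0: 4.5/21 = 21%, a ratio of 4.5/7.5 = 0.60.
- Recorded, r = 0.5: (4.5 + 1.5)/21 = 6/21 = 29%, a ratio of 6/7.5 = 0.80.
- Recorded, r = 1: 36%, a ratio of 1.00.

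With 30% in both groups and r = 0 the figures are 6.3/21 = 30% true and 4.5/21 = 21% recorded.

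The result turns on r, which the article leaves open.

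**The case against.** Four stronger readings are tempting, and the article does not support them.

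- **That people who stop logging in have no safeguard.** The 3-week prompt is written into the safety procedure and targets them. It fires after at most 21 days without activity, about 23% of a 91-day intervention period (21/91).
- **That someone logging in every 20 days slips through.** That person never triggers the flag, but is still on the platform where incidents are entered and can report.
- **That the safety outcome is biased downward, as a fact.** The direction is plausible. The size cannot be derived, and the bias is zero if the prompted contact captures events as well as self-report does.
- **That the progression decision is distorted.** The article says that uptake and safety are not formal progression criteria. Table 2 has no safety threshold, so its result cannot change.

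Other routes may also bring harm to light. The fatigue scale, MSIS-29 and global impression of change are scheduled at 3 and 6 months, interviews extend to those who withdraw, and the CONSORT chart gives reasons for dropout. These bear on whether harm leads to disengagement, but none is an adverse-event record or a listed safety source.

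Finally, the article condenses a fuller protocol, which may set out how events are elicited. Participants are to be asked to report, so it would be wrong to call reporting wholly unprompted. This lowers confidence without removing the point: the article states its safety sources and its schedule outright, and if the full protocol elicits events elsewhere, both need correcting.

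**Conclusion.** The point holds as a limitation of the recording method as written. Non-serious events and expected hospitalisations enter through the platform, no adverse-event enquiry is scheduled, and the inactivity contact is not specified as a place where events are asked about and recorded. Participants who stop using the platform are therefore likely to be under-counted.

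At an assumed 30% who stop, with equal true risk and complete capture among users, the recorded proportion lies between 0.70 and 1.00 of the true one. It would be lower if those who stop have more events and these go uncaptured. These are illustrations of scale, not estimates. What is affected is the descriptive safety result and the recommendation that draws on it. The formal progression rule is not affected. The change is worth making because it is cheap.

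**What to change.** 1. Add a short structured incident question to the existing 3- and 6-month online assessments: falls, fatigue, muscle soreness or sprain, hospital admission, and whether medical care was needed, since the last assessment.
2. Online items alone would still miss people who do not log in. Ask and record the same question in the telephone call already planned ("Participants will receive a telephone reminder if they have not logged on in the 2 weeks prior to the expected assessment completion date") and in the inactivity contact.
3. Reconcile the Safety procedure with the platform-use section on the purpose of the inactivity contact, and list that contact as a safety source in Planned analyses if events are recorded there.
4. Tabulate solicited and spontaneous reports separately, with the number who answered as the denominator for the solicited ones.

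The cost is a few items on existing forms and calls, with no extra visit. The downsides are slightly more participant burden, some recall error over 3 months, and a higher recorded event count, which the report should attribute in part to active questioning.
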